# Effectiveness of CRP-POCT for optimising antibiotic treatment in neonates and children

## **Introduction to sub-study 2 of the Project.**

In this study we intend to investigate if the CRP POCT can be used to screen for viral or bacterial infection, to support appropriate use of antibiotics and become a key in fighting against AMR in low- and middle-income countries.

Antimicrobial resistance (AMR) is estimated to be associated with nearly 5 million deaths, with 1 in 5 deaths occurring in children (1). Globally, bacterial pathogens are increasingly becoming resistant to antibiotics, constituting a significant threat to global health. AMR is more pronounced in children and neonates than in the general population, largely due to the overuse and misuse of antibiotics in these age groups (2). The indiscriminate use of antibiotics in children, both in the health care settings and through over the counter sales in community pharmacies and other medicine outlets, has also fueled the development of resistant strains (3), especially in resource limited settings like Tanzania (4). Combatting AMR in children requires comprehensive strategies that involve among other things; improving health care infrastructures, including diagnostic tests to guide specific antimicrobial therapies (5), regulating antibiotics use (6) and implementing proper infection prevention and control measures (7).

Current practice for diagnosing and testing for suspected bacterial infections in Tanzania, Zanzibar specifically, is mainly full blood picture (8), in contrast to the gold standard test which is blood culture and antimicrobial susceptibility testing (AST) (9). Globally, inflammatory markers are potential alternatives for diagnosis of suspected bacterial infections amongst which are interleukin tests, procalcitonin and C-reactive protein (CRP) testing (10). Testing interleukin and/or procalcitonin is relatively expensive to carry out on a routine basis and it requires sophisticated infrastructures (11). C-reactive protein presents a unique opportunity for use in routine clinical practices as it is relatively cheaper to perform and sustain especially when it is used as a point-of-care (POC) test at the vicinity of attending clinicians' rooms (12,13). CRP testing is already optimized in Tanzania, though it has not yet been fully integrated as a routine diagnostic tool across healthcare settings, and especially in Zanzibar (14–16).

C-reactive protein is an inflammatory biomarker in blood which can serve as a proper diagnostic test to quickly ascertain and establish the likelihood of a bacterial infection. Through POC testing of CRP, health care providers can make more accurate and targeted decisions regarding antibiotic prescription as they wait for a 3-day final culture and AST results (17). However, CRP alone lacks absolute specificity in distinguishing bacterial from non-bacterial infections, as elevated levels can also be observed in non-bacterial conditions such as viral infections, autoimmune diseases, and

other inflammatory states. To improve diagnostic accuracy and antibiotic stewardship, an integrated approach combining serial CRP measurements with microbiological confirmation is increasingly being advocated (18).

We will assess the effectiveness of using the CPR POCT assay for optimizing antibiotic therapy 1) in neonates with or at risk of early onset sepsis (EOS) and 2) neonates with clinical signs of late onset sepsis (LOS) as well as 3) admitted children with febrile illness and diarrhoea.

## **Objectives**

The aim of this study is to determine the feasibility and effectiveness of C-Reactive Protein Point of Care Test in clinical decision making on antibiotic treatment in neonates and children with febrile illness and diarrhoea admitted in Vitongoji Hospital and Mnazi Mmoja Hospital in Zanzibar.

### **Specific objectives**

1. Feasibility
  - a. To assess the feasibility of using CRP POCT in paediatric wards in selected hospital in a low-resource setting
2. Use of CRP in neonates
  - a. To assess the safety and effectiveness of the CRP POCT at 18-24 hours of life guiding initiation of antibiotic therapy in neonates at risk of early onset sepsis
  - b. To assess the safety and effectiveness of the CRP POCT in guiding discontinuation of antibiotic therapy in neonates (0-28 days) admitted with suspected sepsis
3. Use of CRP in children from 6 months to 12 years
  - a. To assess the effectiveness of the CRP POCT in guiding discontinuation of antibiotic therapy in children 6 months to 12 years admitted with fever or diarrhoea
4. Etiology and resistance
  - a. To establish the pathogens and resistance patterns in neonates and children with blood culture proven sepsis

## **Hypothesis**

The hypothesis is that using CRP POCT to support clinical decision on antibiotic treatment of neonatal and pediatric patients in Mnazi Mmoja and Vitongoji hospital will safely help to 1) reduce the use of prophylactic antibiotics in neonates with WHO risk factor of early onset sepsis and 2) ensure adequate and appropriate antibiotic treatment for neonates with sepsis. Furthermore, for children 6 months to 12 years, it is the hypothesis that 3) the use of CRP POCT will help to identify

the majority of children who suffer from non-bacterial infections and assist in withholding or discontinuing antibiotic treatment when no benefit can be expected thus lowering unnecessary use of antibiotics or shorten the duration of use.

## **Methodology**

### **Study design**

This study is a prospective open-label, individual randomised controlled clinical trial with 28 days blinded follow-up conducted in Vitongoji (VT) hospital and Mnazi Mmoja Hospital (MMH) in Zanzibar. Neonates at risk of early onset sepsis, admitted neonates (0-28 days) with clinical signs of sepsis and admitted children (6 months to 12 years) with febrile illness or diarrhoea that are eligible for participation and parents will be asked for informed consent. If informed consent is obtained the child will undergo randomization to intervention: CRP POCT measurement at 18-24 hours of life (at risk of early onset sepsis neonates) or CRP POCT at admittance and after 18-24 hours of treatment. Further treatment and discontinuation of antibiotics will be guided by flowcharts supporting the clinicians decision of treatment, please refer to description of intervention for further details. Participants will be randomly assigned (1:1) to either CRP-guided or standard-of-care antibiotic continuation/discontinuation. Both groups will be followed up by telephone up to 28 days after intervention. The principal investigator will not be aware of the results of the randomisation and follow-up will be blinded as well. CRP-level and treatment data will be recorded and entered in a central database.

### **Study setting**

The project is conducted in Zanzibar, part of the United Republic of Tanzania which has a total population of 1,889,773, with females accounting for 974,281 (52%) and children under 18 years of age accounting for 826,848 (48%) of the population. Zanzibar is composed of two main islands: Unguja and Pemba. The two islands are separated by a channel approximately 50 kilometres (about 31 miles) wide. The healthcare infrastructure comprises over 300 health facilities, including 189 public health facilities, which serve as the backbone of accessible healthcare, and 135 private health facilities (19, 20).

The proposed trial will involve Mnazi Mmoja Hospital (MMH) and Vitongoji (VT) Hospital, which serve catchment populations of 1,346,322 and 543,441, respectively.

The MMH is the only public tertiary hospital in Zanzibar and is located in Unguja Island. It has 570 bed capacity, of which 124 (21.8%) are paediatric beds. There are three units: neonatal wards with 49 beds; non-neonatal children up to 3 years and has 36 beds; and children  $\geq 3$  – 12 years with 36 beds. There are five paediatricians, seven medical doctors, one clinical pharmacist and 44 nurses

(of which 24 nurses are in the neonatal unit). The total number of admissions in 2021 in the paediatric wards was 17800. MMH has laboratory infrastructure for diagnostics services including culture and AST. Laboratory data from May to October (six months) showed a total of 11,395 complete blood counts samples, and 429 blood culture samples were processed.

The VT Hospital is a public district (secondary) hospital located in Pemba Island and is the highest-level care facility on the island. It has a 150-bed capacity and 229 staff of various cadres. Currently only 42 beds are operational due to on-going renovation (of these 10 are paediatric beds). In the paediatric ward, VT has 5 medical doctors, and 2 nurses work in paediatric ward. The total number of admissions in 2021 in the paediatric wards was 818. The laboratory data at VT hospital from May to October 2021 (six months) showed a total of 44 blood samples were received and processed for complete Blood Counts (CBC).

The Public Health Laboratory-Ivo de Carneri (PHL-IdC), (<http://www.phlidc.org/>), an entity of Ministry of Health located in Pemba, Zanzibar, United Republic of Tanzania, is a WHO Collaborating Centre for Neglected Tropical Diseases since 2005. Its activities include assisting relevant programmes to implement disease control strategies, undertaking operational research and strengthening capacities of health staff. PHL-IdC also provides the local population with routine services for selected laboratory tests to compliment Government MoH diagnostic and preventive efforts. It is the only public health laboratory in Pemba capable to carry out the microbiological diagnosis. It supports VT hospital and other hospitals in Pemba for culture and AST.

The microbiology laboratory at Makunduchi Health Centre, established in partnership with the Bernhard-Nocht Institute for Tropical Medicine (BNITM) provides diagnostic infrastructure for the study in Unguja island. This clinical laboratory in Zanzibar provides culture and AST and plays an important role in AMR Surveillance.

## **Study population**

### *Population*

All neonates at risk of/with early onset sepsis, admitted neonates (0-28 days) with suspected sepsis and admitted children (6 months to 12 years) with febrile illness or diarrhoea in VT hospital and MMH are eligible for participation.

### *Inclusion criteria*

Patients meeting the following criteria will be included in the study:

- Between 0-28 days (inclusive) and fulfilling one of two inclusion criteria

- Newborns at risk of early onset sepsis according to the WHO criteria and therefore eligible for prophylactic antibiotic treatment example:
  - a) membranes ruptured over 18 hours before delivery or
  - b) maternal fever (over 38 °C) during labour or
  - c) amniotic fluid is foul smelling or purulent
- All children from day 0 to day 28 admitted with suspected sepsis (clinical signs subjectively judged by the clinician)
- Children between 6 months and 12 years with need of admission with either:
  - a) Febrile illness with temperature above 38 degrees or below 36 degrees at admission, or a history of febrile illness within the last 72 hours
  - b) Diarrhoeal disease (defined as the passage of 3 or more loose or liquid stools per day) with or without fever
- Parents/caregivers of admitted children are able and willing to comply with all study requirements.
- Parents/caregivers of admitted children are able and willing to give voluntary Informed consent.

#### *Exclusion criteria*

- Age >28 days until 6 months
- Severely ill where measurement of CRP POCT would delay the treatment process.
- Neonates who need surgery or have major congenital malformations that will required hospital admission
- Patients with known immunosuppression or severe chronic disease
- Parents/caregivers who are not able to participate in follow-up procedures
- Positive rapid diagnostic test for malaria
- Have taken antibiotics within 24 hours before admittance

#### **Intervention**

CRP POCT equipment will be supplied at the two hospitals MMH and VT hospital, along with a training in use and interpretation supporting the clinical evaluation of the neonate and child.

- a) All included neonates delivered at one of the two hospitals with a risk factor of early onset sepsis as defined by WHO will have a CRP POCT measured at 18-24 hours of life. A measurement below 30mg/L indicates that the neonate does not need antibiotic treatment, CRP levels between 30mg/L and 50mg/L indicate caution and that the neonate should be

assessed clinically and CRP measurement repeated after 6 hours. CRP levels above 50mg/L indicate that the neonate needs antibiotic treatment for early onset sepsis, figure 1.

- b) For neonates admitted with suspected sepsis and randomized to the CRP group, antibiotic treatment should be initiated regardless of CRP levels and if possible including a blood culture. CRP will be reassessed after 18-24 hours of treatment, if both CRPs are below 10mg/L antibiotics are most likely not needed. The treatment is continued until the result of the blood culture, if negative the clinician can consider differential diagnosis and discontinuing the antibiotic treatment if the neonate is well. CRP levels above 100mg/L indicates severe disease and that the clinician should take into consideration meningitis and performing a lumbar puncture, figure 2.
- c) For children 6 months to 12 years admitted with fever, history of fever or diarrhoea and in the intervention group, CRP will be taken at admittance and again at 18-24 hours. It will be communicated that if both CRP levels are less than 10mg/L it indicates that the disease is not severe, and antibiotics are most likely not needed and hence can be either not started or discontinued. If the second CRP is between 10mg/L and 50mg/L, antibiotics might be needed depending on whether the trend of the CRP is upwards or downwards. Hence, if antibiotics have been initiated the clinician can consider stopping the antibiotics earlier. If any of the CRP's are more than 50mg/L that it is likely that antibiotics are needed and treatment should be continued, figure 3. At all times the health care workers are instructed to take the clinical picture into account together with the value of the test. With obvious symptoms of bacterial infection with affected general condition, antibiotic treatment may be initiated and continued on clinical indication. The training of health care workers will also include knowledge of CRP pharmacodynamics and cases where a low CRP might need to be interpreted cautiously, e.g. a history of fever lasting less than 24 hrs. HCWs will be instructed to use CRP POCT for all patients in the intervention group and use the information to guide diagnosis and treatment choice. We will use an appropriate machine procured through the Ministry of Health, for instance Aidian QuickRead go CRP POCT set-up. Feasibility of using the CRP POCT will be assessed using the framework provided by Bowen et al describing acceptability, demand, implementation, practicality, adaptation, integration, expansion, limited-efficacy testing (4).

[figure not shown]

Aidian CRP POCT.

The training of HCWs will include the following flowcharts, figure 1 to 3

[figure not shown]

Figure 1: CRP intervention flowchart for neonates with risk factors of early onset sepsis (EOS)

[figure not shown]

Figure 2: CRP intervention flowchart for neonates with signs of infection

[figure not shown]

Figure 3: CRP intervention flowchart for children with febrile illness or diarrhea

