### **Study endpoints**

The primary study outcome is the duration of antibiotic treatment (number in 24-hour periods between start and end of antibiotic treatment) within 14 days of the admittance of included neonates and children in each study arm (superiority analysis). Antibiotic use during admittance and a composite measure of antibiotic use during admittance and discharge are reported. For every participant, the types and quantity of antibiotics given during the study period will be assessed based on individual drug administration records. To ensure patient safety in case of reduction in antibiotic use a second primary outcome relapse of infection is measured as reinstitution of antibiotics within 72 h after completion of the initial course of antibiotic treatment.

The secondary study outcomes are:

1. Antibiotic use (prescribed daily doses)
2. Choice of antibiotic drug and dose compared to local standard treatment guidelines
3. Number of days admitted in hospital
4. Number of days until resolution of symptoms
5. Development of clinical signs of sepsis
6. Proportion of cases with blood cultures collected before antibiotic treatment
7. Bacterial pathogens and AST in blood cultures
8. Hospital re-admittance within 14 days
9. Mortality at follow up day 7 and 28

Our definition of prescribed and defined daily doses accords with the recommendations of WHO. The route of administration will be incorporated in the daily dose calculations.

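### For neonates with suspected sepsis, the written CRP guidance gives no step after two low CRPs when no blood culture was taken, and none before the culture result

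*Protocol*

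**What the plan says.** Objective 2b (Protocol, Specific objectives) is to assess the safety and effectiveness of the CRP test in "guiding discontinuation of antibiotic therapy in neonates (0-28 days) admitted with suspected sepsis".

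The rule for this group is item b of the Intervention section. It makes three statements in turn:

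- For neonates randomised to the CRP arm, "antibiotic treatment should be initiated regardless of CRP levels and if possible including a blood culture".
- CRP is repeated after 18-24 hours of treatment, and "if both CRPs are below 10mg/L antibiotics are most likely not needed".
- On what happens next, the item reads: "The treatment is continued until the result of the blood culture, if negative the clinician can consider differential diagnosis and discontinuing the antibiotic treatment". A condition that the neonate is well follows.

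The only other CRP level mentioned, above 100 mg/L, concerns severity and not stopping. The item refers to figure 2, the flowchart for this group, which is not shown in the available text.

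The Introduction describes CRP as helping providers decide on antibiotics "as they wait for a 3-day final culture and AST results". Item c, for children, lets two CRPs below 10 mg/L lead to not starting or to stopping antibiotics, with no culture condition.

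**The concern.** The second and third statements of item b do not fit the first. A culture that may not be taken is made the gate to the only discontinuation step in the text. A neonate with two low CRPs and no culture is told both that antibiotics are probably unnecessary and that treatment goes on until a result that will never arrive. Where a culture exists, the CRP at 18-24 hours leads to no step of its own before the result.

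Two things are at stake.

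- **Delivery and adherence.** Study procedures has deviations from CRP recommendations recorded, and Data analysis excludes non-adherers from the per-protocol analysis. For an uncultured low-CRP neonate, neither stopping nor continuing can be coded as adherent from the text.
- **Attribution.** The stop depends on CRP and culture together. The culture prompt in item b is written for the CRP arm, and nothing withholds a negative culture from control clinicians. If culturing differs between arms, a difference in duration cannot be assigned to CRP without knowing culture uptake. If culturing is low, the contrast is diluted.

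**Working it through.** **The rule, case by case (both CRPs below 10 mg/L, text of item b only)**

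| Culture status | What the text offers |
|---|---|
| Taken, negative, neonate well | Discontinuation may be considered |
| Taken, result pending | Continue |
| Not taken | Continue until a result that does not exist; no other step |

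The sentence on continuing could be read as covering every neonate in the group and not only those with low CRPs. The table does not change, because the negative culture is still the only written route to stopping.

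**The plan's own figure**

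Inputs from Sample size calculation: mean 7 days, SD 5 days, 20% reduction (0.20 × 7 = 1.4 days), alpha 0.05 (taken as two-sided), power 90%. Per arm:

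n = 2 × [5 × (1.960 + 1.282) / 1.4]² = 268.05, so 269.

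The Protocol states 262, which is 7 fewer (2.7%). That is close enough to use these inputs. The group target is 646, or 323 per arm; less the assumed 20%, 646 × 0.8 / 2 = 258 per arm.

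**Illustration of dilution**

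Assumptions, none fixed by the Protocol for this group:

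- A low-CRP neonate would otherwise be treated for the overall mean of 7 days.
- The culture result comes at the 3 days given in the Introduction, so a stop there saves 7 − 3 = 4 days.
- Every low-CRP neonate with a culture is culture-negative, well and stopped.
- Neonates without a culture are not stopped early, and controls do not stop on a negative culture.

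Share of the whole CRP arm that must be low-CRP, cultured and stopped to reach 1.4 days: 1.4 / 4 = 35%. For scale only, a saving counted from the second CRP at about day 1 would be 6 days, and the share 1.4 / 6 = 23%.

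Let L be the low-CRP share and c the cultured share among them. Mean saving d = 4 × L × c. Power = Φ(d / [5 × √(2/n)] − 1.960), where 5 × √(2/258) = 0.440 and 5 × √(2/323) = 0.393.

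| L | c | d (days) | Power, 258 per arm | Power, 323 per arm |
|---|---|---|---|---|
| 50% | 100% | 2.0 | 99.5% | 99.9% |
| 50% | 75% | 1.5 | 92.6% | 96.8% |
| 50% | 50% | 1.0 | 62.2% | 72.0% |
| 50% | 25% | 0.5 | 20.5% | 24.5% |
| 30% | 50% | 0.6 | 27.5% | 33.2% |
| 70% | 50% | 1.4 | 88.9% | 94.5% |

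The result turns on L and c, and the Protocol gives neither.

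**The case against.** **Figure 2 may close the gap.** Study design says discontinuation is guided by flowcharts, and staff are trained on them. Figure 2 could hold a branch for neonates without a culture. This stands, and it limits the claim to the text. If such a branch exists, text and figure still disagree and need aligning.

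**The guidance is advice.** A reader might infer that these neonates cannot be stopped, or that the intervention has no stopping step. The Protocol does not support that. Its wording is permissive, staff are told to weigh the clinical picture, and treatment decisions rest with the hospital clinicians. One can also read the culture condition as applying only where a culture exists. But a stop on clinical judgement alone is not a CRP-guided stop, and the text does not state the narrower reading.

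**CRP plus culture may be intended.** The Introduction says CRP alone lacks specificity and favours combining serial CRP with microbiological confirmation, and objective 2b speaks of guiding, not of CRP acting alone. This is fair. A culture condition is a legitimate design, but it sits badly with a culture that is optional and has no stated alternative.

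**Culture uptake is unknown.** A reader might set the two counts in Study setting against each other ("11,395 complete blood counts samples, and 429 blood culture samples were processed") and conclude that few neonates will be cultured and that the effect is out of reach. Those are laboratory totals at one hospital, not restricted to neonates or suspected sepsis, and give no rate for this group. Nor does the secondary outcome "Proportion of cases with blood cultures collected before antibiotic treatment" show that culturing will be incomplete: it measures timing as well as uptake.

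**Much is already recorded.** Study procedures captures treatment decisions, reasons for deviation and all diagnostic tests, and adherence is to be analysed. So the data to detect uneven culturing exist. What is missing is a written rule against which to code adherence in the uncultured.

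**Conclusion.** The point holds for the written CRP guidance. Item b makes the culture conditional, then makes its result the only route to discontinuation after two low CRPs. It therefore gives no CRP-guided step without a culture and none before the result, which fits poorly with objective 2b and with the Introduction's account of CRP as support during the wait.

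This conclusion rests on the text and needs no figure. The statistical size is conditional. The culture condition can weaken the contrast between arms materially (power from 20.5% to 99.5% at 258 per arm as the cultured share runs from 25% to 100%, with half the neonates low-CRP). It does not rule out the planned 1.4 days when most are cultured.

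The 4-day saving is itself an assumption. It subtracts a background 3-day figure from an overall mean, individual savings could be larger, and the mean among low-CRP neonates is not given. Any claim that the planned effect is unattainable goes beyond the documents.

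**What to change.** - Reconcile the sentences of item b with each other, with figure 2 and with objective 2b, so that every neonate with two low CRPs has one defined path whether or not a culture was taken, and adherence can be coded. Which path is for the sponsor to decide.
- If the culture condition stays, describe the strategy tested in this group as CRP plus culture, in objective 2b and in the conclusions.
- Report, by arm, the proportion of neonates with any blood culture taken, beside the duration result. Use the diagnostic tests recorded under Study procedures. The secondary outcome on cultures before antibiotics is not enough alone, because it leaves out cultures taken after treatment starts.

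The cost is Protocol and possibly flowchart wording, plus one table from data already collected. The downside is a narrower claim for this group if the culture condition is kept.
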